## 2. Method and Analysis

### 2.1. Trial Design

This study is a phase 2, dose-finding, double-blind, randomized placebo-controlled trial to evaluate the efficacy and safety of two different doses of USL, compared with a placebo, for DED treatment. The trial will be conducted at Daejeon University Daejeon Korean Medicine Hospital and is set to start recruitment in January 2025. Participants who sign a written informed consent form after receiving a comprehensive explanation of the trial will be screened, and 120 participants will be enrolled after the eligibility assessment. Eligible subjects will be randomized into three groups in a 1:1:1 allocation ratio: standard-dose USL (1 g/day), high-dose USL (2 g/day), and placebo groups. The subjects would be asked to administer one of the medications twice a day for 12 weeks and visit five times (at screening, baseline, week 6, week 12, and week 14) to evaluate the efficacy and safety outcomes (Figure 1, Table 1). This study follows the guidelines of the Standard Protocol Items: Recommendations for Interventional Trials (SPIRIT) [30] and will be conducted in compliance with ethical principles in the Declaration of Helsinki and Good Clinical Practice guidelines [31].

This study protocol was approved by the Institutional Review Board of Daejeon University Daejeon Korean Medicine Hospital (DJDSKH-23-DR-11), and registered at Clinicaltrials.gov (NCT06016010).

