
#### 2.2.3. Sample Size

The estimated sample size required for this trial is 120 patients (40 patients per group), based on previous comparable studies [34,35,36]. Although we could not calculate the sample size based on the exact effect size, as our study is the first trial using USL on patients with DED, we calculated the sample size based on previous studies expected to have similar effects. We assumed the difference in the changes in TBUT as 1.3, and the standard deviation (SD) as 1.8 from baseline to post-intervention between the control and standard-dose USL groups. The power to detect differences is assumed to be 0.8, with the two-sided significance level set at 0.05. The ratio of the allocation of subjects between groups is 1:1:1, and the dropout rate is assumed to be 0.2.

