##### Tear Break-Up Time (TBUT)

TBUT was chosen as the primary outcome for objective signs in our study because TBUT assesses tear film stability, which is one of the essential diagnostic criteria for diagnosing tear film abnormalities and DED [37]. TBUT is also one of the most frequently used diagnostic tests in clinical practice for DED [38].

The procedure follows a standardized methodology. For the TBUT test, subjects will be instructed to sit at the slit-lamp microscope with their chin on the chin rest. Sodium fluorescein will then be applied to both eyes on the inferior temporal bulbar conjunctiva. Each participant will be instructed to blink naturally three times to distribute fluorescein on the ocular surface. Then, the participants will be asked to cease blinking until instructed otherwise. The time between eye opening and the first appearance of a dry spot in the tear film will be measured in seconds using a slit-lamp microscope (BQ-900; Haag-Streit, Bern, Switzerland). The cut-off value of TBUT for the diagnosis of DED is reported to be less than 10 s for an abnormal tear film, between 5 s and 10 s for a marginal tear film, and less than 5 s for severe DED [39]. With reference to this, participants with a TBUT ≤ 10 s will be included in this trial. The TBUT for each participant will be measured at screening, week 6, week 12, and week 14, and we will measure the changes in mean TBUT from screening to week 12 between the intervention and control groups as the primary outcome.

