##### Ocular Surface Disease Index (OSDI)

The OSDI is the primary outcome measure of subjective symptoms in this trial. It is the most commonly used questionnaire for patients with DED in clinical trials. The OSDI has been validated to measure the severity of DED, and it comprises psychometric symptoms related to DED [40]. Owing to its strong establishment in DED, a consensus to use the OSDI was reached by a related committee [15].

The OSDI measures the frequency of symptoms, environmental triggers, and vision-related quality of life within 1 week. It comprises 12 questions, each of which is graded on a scale of 0–4, where 0 indicates none of the time, 1 as some of the time, 2 as half of the time, 3 as most of the time, and 4 as all of the time [40]. The total OSDI score is calculated as follows: OSDI = [(sum of scores for all questions answered) × 100]/[(total number of questions answered) × 4]

Thus, the OSDI score ranges from 0 to 100; the higher the score, the worse the quality of life. According to OSDI scores, patients can be categorized as having normal (0 to 12 points), mild (13 to 22 points), moderate (23 to 32 points), or severe (33 to 100 points) ocular surface disease. In our trial, patients with OSDI scores ≥ 23 points will be included, meaning that those who have moderate-to-severe symptoms will all be included. The OSDI score will be measured at screening, week 6, week 12, and week 14, and the changes in OSDI from screening to week 12 will be the primary outcome of this trial.

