### 2.7. Statistical Analysis

Statistical analyses of all outcomes will be conducted by an independent statistician using SAS Version 9.4 Analytics Pro software. Continuous variables will be presented as the mean ± SD and categorical variables will be presented as frequencies and percentages. For efficacy analysis, a full analysis set (FAS) based on intention-to-treat (ITT) analysis will be performed as the primary analysis, and PP analysis will be used for secondary analysis. All randomized participants who are evaluated at least once after administration of the trial medication will be included in the FAS, and only those who complete the trial without violating the protocol will be included in the PP set. A safety analysis will be conducted for all participants who are randomized and administered the trial medication at least once.

The primary and secondary efficacy outcomes will be analyzed using the mixed-effects model for repeated measures, with each group and visit set as fixed effects and participants as random effects. In addition, the difference between pre- and post-treatment within groups will be analyzed using Student’s paired *t*-test or Wilcoxon signed-range test, depending on normality. A multiple imputation method will be used for missing values. The efficacy of USL will be accepted at a significance level of 2.5% in both TBUT and OSDI compared with the placebo, whereas other secondary outcomes will be accepted at a 5% significance level.

To analyze safety outcomes, Fisher’s exact test will be used to compare the number of AEs between the groups, and Student’s paired *t*-test or the Wilcoxon signed-rank test will be performed to analyze the differences between pre- and post-treatment laboratory variables, vital signs, visual acuity, and IOP. Demographic characteristics will be analyzed using the Wilcoxon rank-sum test or independent *t*-test for continuous variables and Fisher’s exact test or the chi-square test for categorical variables.

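### Read literally, the primary mixed model is a random-intercept model, whose equal-variance and equal-correlation assumption suits the screening-to-week-12 contrast poorly; state the covariance, the contrast and the role of screening

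*Protocol article*

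**What the plan says.** Section 2.7 of the protocol article fixes the model type: "The primary and secondary efficacy outcomes will be analyzed using the mixed-effects model for repeated measures". It then lists the terms: "with each group and visit set as fixed effects and participants as random effects". It mentions no residual covariance structure, no group-by-visit term and no role for the screening value.

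The primary outcomes are defined at one visit. For TBUT, "we will measure the changes in mean TBUT from screening to week 12 between the intervention and control groups as the primary outcome". For OSDI, "the changes in OSDI from screening to week 12 will be the primary outcome of this trial".

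The reading times are unevenly spaced. "The TBUT for each participant will be measured at screening, week 6, week 12, and week 14", and OSDI follows the same schedule. Table 1 places screening at week -2.

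**The concern.** A participant random effect with independent residuals implies compound symmetry. Two readings 2 weeks apart (weeks 12 and 14) are then taken to be as strongly correlated as two readings 14 weeks apart (screening and week 12). If correlation in fact fades with time, the model averages the small short-gap variability with the larger long-gap variability. It then applies that average to the longest-gap contrast that matters, the primary one.

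Equal variance is also doubtful. Section 2.2.1 restricts screening values (TBUT at most 10, OSDI at least 23), and later readings are not restricted.

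At stake is the 2.5% level at which section 2.7 accepts efficacy on TBUT and OSDI. A standard error that is too small for the week-12 contrast would make the p-value too small.

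**Working it through.** **Inputs from the article.** Readings at weeks -2, 6, 12 and 14, so the six gaps are 8, 14, 16, 6, 8 and 2 weeks. Test level 2.5% (section 2.7), taken here as two-sided, z = 2.2414. SD of change 1.8, difference 1.3, dropout 0.2, 40 per group (section 2.2.3).

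**Inputs assumed.** All correlations and all visit-specific SDs; the article gives none.

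**1. The plan's own figure.** n per arm = 2 × (1.960 + 0.842)² × (1.8/1.3)² = 30.1, so 31. The t-based version gives 32. Then 32/0.8 = 40 per arm and 120 in total, as stated. The simulations below use 32 completers per arm.

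**2. Formula.** With complete data a random-intercept fit estimates the residual variance as the mean variance minus the mean covariance over visits. For a week-12-minus-screening contrast:
- model variance = 2 × (mean variance − mean covariance)
- true variance = V(screening) + V(week 12) − 2 × Cov(screening, week 12)
- actual level = 2 × [1 − Φ(2.2414 × √(model/true))]

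**3. Worked case, screening as a response visit.** Assume correlation 0.8 × exp(−weeks/30) and unit SDs. The six correlations, in the order of the gaps above, are 0.613, 0.502, 0.469, 0.655, 0.613 and 0.748, mean 0.600.
- Model variance: 2 × (1 − 0.600) = 0.800.
- True variance: 2 × (1 − 0.502) = 0.997.
- True/model = 1.25; standard-error ratio √(0.800/0.997) = 0.896. A true SD of change of 1.8 is treated as 1.8 × 0.896 = 1.61.
- Actual level: 2 × [1 − Φ(2.008)] = 4.5%.

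In 20,000 simulated trials the random intercept ran at 4.4% and an unstructured covariance at 2.4%.

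**4. Same case, change scores at weeks 6, 12 and 14 as the response.** The change variances are 0.775, 0.997 and 1.061, mean 0.944. The ratio is √(0.944/0.997) = 0.973 and the level is 2.9%. With screening as a covariate it is 2.8%.

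**5. Range over assumptions (actual level at nominal 2.5%).**

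| Assumed pattern | Screening as response visit | Change score or covariate |
|---|---|---|
| 0.8 × exp(−weeks/30), equal SDs | 4.5% | 2.8-2.9% |
| Same, screening SD 0.8 / 0.7 of later SDs | 3.7% / 3.4% | 2.8-2.9% |
| Exponential decay, 14-week correlation 0.3 to 0.7, equal SDs | 5.8-6.8% | 2.9-3.2% |
| Decay with short-gap limit 0.8, 14-week correlation 0.3 to 0.5, equal SDs | 4.5-4.7% | 2.8-2.9% |
| Equal correlation, equal SDs | 2.5% | 2.5% |
| Equal correlation 0.3 to 0.5, screening SD 0.7 of later SDs | 1.6-1.7% | 2.5% |
| Equal correlation 0.3 to 0.5, later SDs 1.2 times screening | 1.9-2.0% | 2.5% |

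Over all decay patterns and screening SD ratios tried, the ranges are about 3-7% and 2.7-3.3%. These keep the post-baseline SDs equal. With equal correlation but unequal post-baseline SDs, the change-score and covariate versions moved either way, from 1.6% to 3.5%.

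**6. The contrast itself.** With group and visit as main effects only and screening in the response, the group coefficient averages over four visits. A constant post-baseline effect of 1.3 would appear as 1.3 × 3/4 = 0.975, which is not the declared week-12 change.

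**The case against.** The strongest reply is that the defect is inferred. Section 2.7 does not say that the participant effect is the only within-participant term. The model's name is compatible with a structured residual matrix, and a journal article may leave the covariance structure and degrees-of-freedom method to the full protocol or SAP. This stands as far as it goes: silence on those details is not itself the point. But the section does state a within-participant structure, and a programmer who followed it literally would fit compound symmetry.

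A second reply is that the larger figures need a group-by-visit term, which section 2.7 does not list, and screening as a response visit, when the outcomes are worded as changes. Both stand. With change scores the effect is minor. With main effects only and complete data, the test of the visit-averaged group effect is unaffected, although that is not the declared outcome. The article leaves open which version is meant.

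Third, the two grounds for doubt partly offset each other. A smaller screening variance shrinks the inflation under decay, and with equal correlation it makes the test conservative. This stands too.

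A reader might also infer that dropout makes matters worse, because a wrong correlation misweights incomplete participants. The article does not support giving that weight: section 2.7 plans multiple imputation, so the imputation model would largely govern how those participants contribute.

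**Conclusion.** The point holds in a limited form. On a literal reading the stated model assumes equal variance and equal correlation over unevenly spaced visits, and the primary contrast is one for which that assumption matters. If correlation decays with time, a nominal 2.5% test would run at about 3-7% with screening as a response visit, and at about 2.7-3.3% with change scores or screening as a covariate. The error is nil under equal variance and correlation. The test is conservative, about 1.6-2.0%, under equal correlation with the smaller screening variances tabulated.

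A reader might conclude that the week-12 standard error is too small, or that the model rules out any other covariance. The article supports neither. It gives no correlations or visit-specific variances, and it does not exclude a further residual structure. Size and direction both rest on assumptions and on how screening enters. The change is still worth making: the sentence as written does not suit the declared outcome, and the remedy costs almost nothing.

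**What to change.** In section 2.7, replace the participant random effect with repeated visits within participant under an unstructured covariance matrix and Kenward-Roger degrees of freedom. Name one fallback for non-convergence, for example heterogeneous Toeplitz with robust standard errors. In the same place, add the group-by-visit term, define the primary test as the week-12 contrast of each USL dose against placebo, and say whether the screening value is a covariate or is subtracted as a change score.

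Cost: one sentence in the protocol or SAP before unblinding, a few degrees of freedom and no new data. With three post-baseline visits the unstructured matrix has 6 parameters against 2, so four extra. If screening is kept as a fourth response visit it has 10 against 2, so eight extra. If an unstructured matrix is already intended, stating it costs nothing.

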## 3. Discussion

Despite the growing burden of DED on public health, current treatments for DED present unmet medical needs owing to their side effects or ineffectiveness. Clinicians and patients with DED seek better treatment therapies to manage inflammation and ocular symptoms; nutritional supplements or complementary medicine have emerged as promising candidates for DED by managing ocular surface inflammation [51]. As inflammation is recognized as a major factor in the pathogenesis of DED, we anticipate that the anti-inflammatory effects of USL would improve the symptoms and signs of DED.

Our trial was designed to evaluate the efficacy and safety of USL for DED compared with a placebo and to determine the appropriate dosage of USL. We plan to conduct a phase 2, double-blind, dose-finding, randomized placebo-controlled trial, and both objective signs and subjective symptoms of DED, as well as cytokines related to inflammation, will be investigated. Objective signs and subjective symptoms are important in the diagnosis and management of DED; however, previous studies have reported a lack of association between them, making DED more complicated. The Food and Drug Administration (FDA) recommends that the efficacy of treatment should be demonstrated by showing significant differences in objective prespecified signs and subjective prespecified symptoms of dry eye. Moreover, the FDA suggests that different endpoints for objective signs (conjunctival staining, corneal staining, Schirmer’s test score, and TBUT) or subjective symptoms should be conducted when designing clinical trials for the treatment of DED. According to the FDA guidelines, we will evaluate TBUT and OSDI as primary outcomes and other objective endpoints, including fluorescein corneal staining score, Schirmer’s test, meibomian gland test, and subjective endpoints of VAS and SPEED-II as secondary outcomes. In addition, to investigate the inflammatory effects of USL, cytokines IL-1β, IFN-γ, and TNF-α will be measured.

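### The primary decision rule does not say which dose decides, or whether the 2.5% level is shared over the two endpoints or the two doses

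*Protocol article*

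**What the plan says.** Section 2.1 randomises patients 1:1:1 to standard-dose USL, high-dose USL and placebo. Section 2.6.1 names TBUT and OSDI as the primary outcomes. That makes four possible primary comparisons with placebo, and the article describes them in three different ways:

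- Section 2.7, the acceptance rule: "The efficacy of USL will be accepted at a significance level of 2.5% in both TBUT and OSDI compared with the placebo". The same sentence adds that "other secondary outcomes will be accepted at a 5% significance level".
- Section 2.2.3, the sample size: a TBUT difference "from baseline to post-intervention between the control and standard-dose USL groups", with "The power to detect differences is assumed to be 0.8, with the two-sided significance level set at 0.05".
- Section 2.6.1, under TBUT: "changes in mean TBUT from screening to week 12 between the intervention and control groups as the primary outcome".

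The Discussion explains the choice of a sign and a symptom by regulatory guidance that efficacy be demonstrated by "showing significant differences in objective prespecified signs and subjective prespecified symptoms of dry eye".

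**The concern.** The rule speaks of USL as if there were one active arm. Nothing in the article says whether success at one dose is enough, whether both doses must succeed, or whether one named dose decides. The purpose of the 2.5% is also unstated, and each explanation leaves a gap:

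- If it is 5% divided over two endpoints, either endpoint can win alone and nothing is reserved for the second dose.
- If both endpoints must win, no division over endpoints is needed. The 2.5% then makes sense only as a division over doses, which the text does not say.
- If the standard dose alone decides and both endpoints must win, no division is needed at all.

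The same results could therefore support different conclusions. A high dose significant on both endpoints beside a standard dose that is not would be a success if either dose counts and a failure if both must pass. The level in the rule also differs from the two-sided 0.05 used for sizing.

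**Working it through.** **Inputs.** From 2.2.3: TBUT difference 1.3, SD 1.8, two-sided 0.05, power 0.8, dropout 0.2, 40 per arm. From 2.7: level 2.5%, taken as two-sided because 2.7 does not restate sidedness. With equal arms and a shared placebo, the two dose-versus-placebo statistics have correlation 0.5. The TBUT–OSDI correlation r is not given, so a range is assumed. The Discussion reports a lack of association between signs and symptoms, which points to the low end.

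**1. The plan's own sample size.** n = 2(z₁₋α/₂ + z₁₋β)²(SD/Δ)² = 2(1.960 + 0.842)²(1.8/1.3)² = 30.1, so 31 per arm, and 31/0.8 gives 39. The t-test version needs 31.1, so 32, and 32/0.8 = 40. The stated 120 is reproduced at two-sided 0.05 for one contrast and one endpoint.

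**2. If either endpoint at either dose counted.** There are four two-sided 2.5% tests with critical value 2.241. The error is 1 − P(all four |Z| < 2.241), from the joint normal distribution:

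| r (assumed) | Family-wise error |
|---|---|
| 0 | 9.1% |
| 0.3 | 8.9% |
| 0.5 | 8.5% |
| 0.8 | 7.4% |

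The Bonferroni ceiling is 4 × 2.5% = 10%. If the 2.5% were one-sided, the error would be 8.9% at r = 0 and 8.1% at r = 0.5.

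**3. If both endpoints are required for a dose and either dose counts.** There are two ways to succeed.

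- One endpoint certain to win, the other null at both doses: 1 − P(|Z₁| < 2.241, |Z₂| < 2.241) with correlation 0.5 = 4.65%.
- A different endpoint null at each dose, uncorrelated: 1 − 0.975² = 4.94%.
- Ceiling: 2 × 2.5% = 5%.
- No effect on either endpoint at either dose: 0.1% at r = 0 and 1.4% at r = 0.7.

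The family is controlled. Holding the second dose at 2.5% after the first has passed is stricter than control at 5% requires.

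**4. Power at the decision level.** With 40 × 0.8 = 32 evaluable per arm, the expected statistic is (1.3/1.8) × √(32/2) = 2.889.

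- TBUT alone at 5%: Φ(2.889 − 1.960) = 82%.
- TBUT alone at 2.5%: Φ(2.889 − 2.241) = 74% (72% by t-test).
- For 80% on TBUT alone at 2.5%: n = 2(2.241 + 0.842)²(1.8/1.3)² = 36.4, so 37 evaluable, 37/0.8 = 47 per arm, 141 in total.

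Assuming the same standardised effect for OSDI and for both doses, per-dose power with both endpoints required, by simulation, is:

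| r (assumed) | Each dose at fixed 2.5% | Holm over doses |
|---|---|---|
| 0 | 0.55 (0.741² = 0.55) | 0.61 |
| 0.5 | 0.61 | 0.67 |

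**5. How often the missing dose rule would matter.** Under the same assumptions at fixed 2.5%, exactly one dose passes in about 33–36% of trials. In those trials, counting either dose and requiring both doses give opposite answers.

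**The case against.** A reader might infer that the plan has four ways to succeed and a family-wise error of 8.5–9%. The documents do not support that as a statement about the plan. The wording of 2.7 asks for the level to be met in TBUT and OSDI together, and the Discussion ties the two endpoints to a sign-and-symptom standard. On that reading there are at most two ways to succeed and the error stays within 5%. The inflated figure belongs to a second reading. That reading remains possible because the same sentence gives secondary outcomes a level that attaches to each outcome separately, and because 2.5% is what dividing 5% by two endpoints yields.

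A reader might also treat the standard-dose contrast in 2.2.3 as the deciding test. The section uses it only to calculate the number of patients, which is ordinary in a multi-arm trial. A pooled-dose test is likewise unlikely, since the aim is to find a dose and 2.7 models each group.

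It can further be said that testing order is commonly left to the full protocol or analysis plan, and that an exploratory phase 2 trial, with confirmation planned later, does not clearly need strict control over doses. Both points lower the stakes. They do not remove the problem: the article does state an acceptance rule with a specific level, and as worded it cannot be applied to a three-arm trial without a further choice.

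**Conclusion.** The point holds as an ambiguity in the primary decision rule, not as a demonstrated inflation of error. Under the better-supported reading, with both endpoints required and each dose at 2.5%, the family-wise error is about 4.6% when the same endpoint is null at both doses and cannot exceed 5%. The cost there is lost power: about 0.55–0.61 per dose against 0.61–0.67 with Holm. The error reaches about 8.5–9% only if one endpoint may win alone at either dose, with r between 0 and 0.5. Separately, the sizing level of two-sided 0.05 does not match the decision level of 2.5%, so the stated power of 0.8 does not describe the test in 2.7. The error rates rest on normal approximations and an assumed r. The joint power figures also rest on an OSDI effect that the article does not give.

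**What to change.** Before unblinding, replace the acceptance sentence in 2.7 with a rule such as this:

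*Each USL dose is compared with placebo at week 12. A dose succeeds only if TBUT and OSDI are both significant; its p-value is the larger of its two two-sided p-values. The two dose p-values are tested by Holm's procedure at an overall two-sided 5%: the smaller at 2.5% and, if it passes, the other at 5%. Efficacy is claimed for each dose that passes.*

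Name the same two contrasts in 2.2.3 and 2.6.1. This attaches the 2.5% to the doses and keeps the sign-and-symptom standard. Holm is never less powerful than a fixed 2.5% for each dose.

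In 2.2.3, state an OSDI assumption and restate the power at the decision level: about 74% for TBUT alone at 2.5% with 32 evaluable per arm, and about 0.61–0.67 per dose for both endpoints under Holm, on the assumptions given above.

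The rule needs only wording changes, with no extra patients or data. Its price is that efficacy can no longer be claimed on one endpoint alone. It does not restore 80% power. The sponsor would have to accept and report the lower figure or enlarge the trial.

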#### 2.6.4. Safety Outcomes

Adverse events (AEs), vital signs, laboratory examinations, visual acuity, and IOP will be assessed throughout the trial to evaluate safety. At every visit, AEs, vital signs, visual acuity, and IOP will be observed, and laboratory tests will be performed before and after taking the trial medication. We will record every unexpected symptom or sign during the trial by asking the participants questions and through the investigator’s examination. However, if serious AEs occur during the trial, the patient will be immediately removed from the trial and proper treatment will be provided. Visual acuity and IOP will be examined as recommended by the Ministry of Food and Drug Safety in Korea for clinical trials on ocular diseases. The laboratory tests will include liver function, routine blood, and urine tests.

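### Laboratory values, vital signs, visual acuity and IOP are tested only pre versus post, so neither USL dose is formally compared with placebo on them; the unit for the AE test also needs stating

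*Protocol article*

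**What the plan says.** Section 2.1 (Trial Design) states the purpose as evaluating efficacy and safety of two USL doses against placebo, and section 3 (Discussion) repeats it. Section 2.7 (Statistical Analysis) then fixes the safety methods in one sentence with two parts.

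- **AEs:** Fisher's "exact test will be used to compare the number of AEs between the groups".
- **Continuous safety measures:** a choice between the paired t-test and its rank-based counterpart, both used for one purpose: "to analyze the differences between pre- and post-treatment laboratory variables, vital signs, visual acuity, and IOP".

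The methods in section 2.7 that do compare arms are assigned elsewhere: "The primary and secondary efficacy outcomes will be analyzed using the mixed-effects model for repeated measures", and "Demographic characteristics will be analyzed using the Wilcoxon rank-sum test or independent" t-test.

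The safety population is defined: "A safety analysis will be conducted for all participants who are randomized and administered the trial medication at least once". On data collection, section 2.6.4 (Safety Outcomes) says "At every visit, AEs, vital signs, visual acuity, and IOP will be observed", and for AEs "We will record every unexpected symptom or sign during the trial". Table 1 places laboratory tests at screening and week 12.

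**The concern.** A paired or signed-rank test asks whether the average change differs from zero. In a 12-week trial that change can contain regression to the mean after screening on eligibility limits (IOP, liver enzymes, creatinine, blood pressure and glucose all have one), seasonal or assay drift, and placebo response, as well as any drug effect. The placebo arm exists to remove everything except the last, and the stated test does not use it.

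Two errors follow. A drift shared by all arms can be reported as a change on USL. A real difference from placebo can be missed if placebo and drug move in opposite directions and neither change is individually significant. Setting a significant arm beside a non-significant one does not repair this, because it is not a test of their difference.

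The efficacy paragraph shows the contrast. There, paired tests supplement a model containing group and visit. For continuous safety data they stand alone.

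The AE issue is smaller. Fisher's exact test needs independent units, each with or without the event. If AEs themselves are counted, one participant can enter several times.

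**Working it through.** **Arm size.** Section 2.2.3 gives a TBUT difference of 1.3, SD 1.8, power 0.8, two-sided 0.05 and 20% dropout. Normal approximation: n = 2 × (1.960 + 0.842)² × (1.8/1.3)² = 2 × 7.85 × 1.917 = 30.1, so 31 per arm; 31/0.8 = 38.75, so 39. The t-based solution is 31.09, so 32, and 32/0.8 = 40 per arm, 120 in total. The stated 40 per group reproduces and is used below. The document gives no figure for the safety tests.

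**Is there a between-arm test for continuous safety data?**

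| Method in section 2.7 | Compares arms? | Applied to |
|---|---|---|
| Mixed model, group and visit | Yes | Primary and secondary efficacy |
| Independent t-test or rank-sum | Yes | Demographics |
| Fisher's exact test | Yes | AEs; categorical demographics |
| Paired t-test or signed-rank | No | Efficacy within groups; laboratory values, vital signs, acuity, IOP |

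None is named. The paragraph on safety does not say whether the paired tests are run by arm or pooled, but neither version compares USL with placebo.

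**What the paired test does when there is no drug effect.** Assume every arm shifts by the same s, in SD units of change. The range 0.2 to 0.5 is an assumption.

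By hand, with 40 per arm and a critical t of 2.02 (39 df), the expected t is s√40.
- s = 0.2: expected t 1.26; Φ(1.26 − 2.02) = Φ(−0.76) ≈ 0.22.
- s = 0.5: expected t 3.16; Φ(3.16 − 2.02) = Φ(1.14) ≈ 0.87.

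By simulation, 20,000 trials, 40 per arm:

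| s | Given USL arm significant | That arm significant, placebo not | Between-arm t-test |
|---|---|---|---|
| 0 | 4.8% | 4.6% | 4.9% |
| 0.2 | 23.3% | 18.0% | 4.8% |
| 0.3 | 45.7% | 24.9% | 4.9% |
| 0.45 | 79.4% | 16.7% | 5.0% |
| 0.5 | 86.9% | 11.1% | 5.1% |

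With 32 per arm after 20% dropout, the first result column runs from 19.4% (s = 0.2) to 78.3% (s = 0.5). With no drift the paired test holds its level, so the problem is the shared drift.

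**AE unit.** With identical AE distributions in two arms of 40, Fisher's test on participants with at least one AE rejects in about 3% of trials. For event counts the result depends on assumptions. An exact conditional test on event totals rejects in about 4% if counts are purely Poisson. Fisher's test on events out of 40 rejects in 7% to 13% (Poisson, mean 0.3 to 0.5 per person) and in 20% to 46% with strong clustering within participants (negative binomial, k = 0.3 to 0.15; counts capped at 40). The document gives neither AE rate nor clustering, so no single inflation figure can be attached to this trial.

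**The case against.** The strongest defence has four parts.

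1. **AEs are compared between groups.** A reader might infer that the trial never sets safety against placebo at all. The text does not support that: Fisher's test is a between-group comparison. The gap is confined to the continuous measures.
2. **The AE phrase may be shorthand.** A reader might infer that the plan commits to treating repeat AEs as independent. It does not say so. Fisher's test needs a count without the event, and the same section reports categorical variables as frequencies and percentages; both fit participants as the unit, for which the test is valid. This stands, and it reduces the AE point to a clarification.
3. **Multiplicity does not help the criticism.** One might argue that 10 to 20 laboratory variables give at least one chance finding per arm in 1 − 0.95^10 = 40% to 1 − 0.95^20 = 64% of trials. The number of variables is not stated, independence is assumed, and the same arithmetic applies to between-arm tests. It is no argument for one over the other.
4. **Detail may sit in an unseen SAP, and nothing hangs on these p-values.** Shift tables and AEs by type are commonly left there, so their absence is no finding. Means and SDs may well be tabulated by arm. Acceptance of efficacy is tied to TBUT and OSDI, not to any safety test.

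None of this answers the main point. The article is not silent on continuous safety data; it names tests, and an SAP that followed it would inherit tests that do not address the stated aim.

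**Conclusion.** The point holds for laboratory values, vital signs, acuity and IOP. That the named tests cannot compare arms follows from what they are and needs no assumption. That nothing else fills the gap follows from the allocation of methods in section 2.7. The 23% to 87% false-flag rate, against about 5%, rests on an assumed shared drift of 0.2 to 0.5 SD and 40 per arm; the direction does not depend on those values, and with zero drift the rates coincide.

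For AEs the conclusion is only that the unit should be stated, with no claim about actual type I error.

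The change should be made because safety of two doses against placebo is a stated objective. It does not touch the primary efficacy analysis, the sample size or data collection.

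**What to change.** In section 2.7, replace the paired and signed-rank tests as the safety analysis of laboratory values, vital signs, acuity and IOP. Use the difference in change from baseline between each USL dose and placebo, adjusted for the baseline value (analysis of covariance), with a 95% CI. Keep pre-post changes by arm as descriptive summaries without tests.

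The interval will be wider than a within-arm one. Before baseline adjustment, its half-width is about 1.99 × √(2/40) = 0.44 SD of change, against 2.02/√40 = 0.32 SD within one arm. That is the honest precision for a comparison with placebo.

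In the AE sentence, state that Fisher's exact test compares the number of participants with at least one AE, and that event counts are listed descriptively.

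Cost: two sentences of wording and slightly more output from data already collected. No new visits, participants or measurements.
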